## Abstract

**Background:**

Chronic HIV infection commonly affects both cognition and mental health, even with excellent systemic viral control. The causes of compromised brain health are likely to be a multi-factorial combination of HIV-related biological factors, co-morbidities such as aging and cerebrovascular disease, and the erosion of coping skills, physical health, and social supports resulting from the strains of living with a chronic illness.

**Methods/design:**

This study aims to provide a better understanding of the relationship between cognitive complaints, depression, and objectively measured cognitive impairment in HIV, and of the key factors, whether biological or personal, which relate to these presentations and to their evolution over time. Characterization of this heterogeneity will permit more focused pathophysiological studies, and allow more targeted interventions. The project makes extensive use of Web-based research and health care delivery tools, aiming to provide cost-effective, “clinic ready” tools to improve brain health in HIV. This project has two overarching aims, reflecting our dual goals of understanding and improving brain health in HIV, focusing on cognitive impairment, its contributors and consequences.

The objectives are to contribute evidence for the validity of a brief brain health assessment, to estimate the extent to which HIV-related cognition-relevant clinical factors and patient-centered outcomes inter-relate and evolve over time, allowing identification of the mechanisms underpinning longitudinal change in brain health and to contribute evidence for the feasibility, effectiveness potential, acceptability, and underlying mechanisms of promising interventions for optimizing brain health. We adopt a cohort multiple randomized control trials design. A total of 900 participants will be characterized prospectively over a 27-month period to answer questions about the evolution of outcomes of interest. All participants will be offered basic brain health self-management information. Sub-groups will participate in pilot studies of specific, more intensive interventions to provide pragmatic evidence for feasibility, effectiveness, and comparative effectiveness.

**Discussion:**

This work will provide needed estimates of the burden, heterogeneity, evolution, and mechanisms underlying compromised brain health in HIV, and test a range of promising non-pharmacological interventions. This is an on-going study; the trials nested within this cohort that are currently recruiting participants were registered on 7 October 2015 (Clinicaltrials.gov NCT02571504 and NCT02571595).

## Background

People living with HIV worry about their memory, with good reason. As their life expectancies increase, it is becoming clear that both cognition and mental health can be affected, even with excellent systemic viral control. Although we are only beginning to understand these emerging co-morbidities, they are likely the result of multiple interacting processes. Various mechanisms have been proposed, directly or indirectly related to HIV. HIV infects cells within the central nervous system (CNS), highly active anti-retroviral therapy (HAART) varies in its CNS penetrance, providing a potential reservoir for viral replication, and local or systemic inflammation may affect brain function [1, 2]. Antiretrovirals may themselves be neurotoxic [3–5], and common co-morbidities such as cerebrovascular disease, substance abuse and hepatitis C infection can take their own toll on brain function. Finally, the experience of living with chronic infection can threaten brain health by affecting stress levels, coping, physical health, and social supports. Mood disorders can affect cognition even in otherwise healthy individuals [6], and in HIV specifically, self-reported cognitive concerns have been associated with depressive symptoms [7]. It may be that depressive symptoms and cognitive difficulties are two facets of brain dysfunction, or that depression affects cognitive performance through effects on attention or motivation [8]. This project acknowledges the potential inter-relationship between cognition and mood in HIV, addressing these together within a holistic framework of brain health.

Although the burden of poor brain health in HIV in Canada is unknown, it is likely to be high. Recent studies in other developed countries, using comprehensive neuropsychological assessment, report a prevalence of (primarily mild) HIV-associated neurocognitive disorders (HAND) of 30–50 % [9, 10]. Even higher rates have been documented in those over the age of 50, a rapidly expanding group at the frontier of existing knowledge about the combined effects of aging and longstanding HIV infection [11]. Depression is also common in HIV infection, with population-based prevalence of major depressive disorder estimated as high as 36 % [12]. Impaired cognition and depression, whether together or separately, strike patients in their productive years, and can affect medication adherence, occupational and social function, quality of life, and even accelerate mortality [4, 13–18]. Progress in understanding the heterogeneous, multi-factorial nature of compromised brain health in HIV requires careful clinical characterization, including of its evolution over time, accompanied by hypothesis-driven research focused on specific clinical phenotypes. Progress in predicting, treating and mitigating the impact of poor brain health requires better, practical clinical tools and evidence-based interventions specifically tailored for people living with HIV.

The nomenclature describing cognitive impairment, and the modalities used to measure cognition vary across clinical disciplines, hindering interdisciplinary research. Here, we have chosen to use the term cognitive deficit and its positive opposite, cognitive ability; we also distinguish between directly measured cognitive deficits (i.e. neuropsychological tests) and perceived cognitive deficits reported as symptoms (here measured using validated questionnaires). This method is broadly consistent with the requirements of the current diagnostic criteria for HAND [3]. Our view of cognition departs from current categorical diagnosis, focusing instead on cognitive ability as a “quantity” [19]. We propose that declines in cognitive ability compared to the individual’s own baseline will be the most useful trigger for intervention, and that stability or improvements are likely to be more important to the patient than whether they meet strict diagnostic thresholds. Rigid use of diagnostic categories may prevent recognition of real difficulties, and limit access to useful interventions for patients with high (but deteriorating) cognitive abilities [20, 21].

Current approaches to diagnosis of HAND rely on neuropsychological testing [3]. This is resource-intensive, with restricted availability. Front-line health care providers who must judge whom and when to refer are poorly equipped to respond to patients’ concerns about cognition: What symptoms signal difficulties that warrant further investigation or intervention? What interventions are appropriate? Are there patients who do not report symptoms who nonetheless have deficits and would benefit from assessment and treatment? We recognize that a key challenge in this area is to understand the link between what patients are saying, which is what matters to them, and what the objective tests indicate. Further, we need to better understand the relationship between different facets of brain health, address these within an interdisciplinary framework, and characterize their evolution over time. Developing better ways to measure both symptoms and signs that are feasible in everyday practice and tuned to the full range of abilities in this population is a crucial first step.

While better measurement and thorough description of the clinical phenomenology and its temporal evolution are necessary, they are not sufficient. People with HIV cannot afford to wait for researchers to fully understand the multiple factors that are likely to underpin the brain health challenges they are facing now. Research on the effects of exercise, self-management and cognitive training in healthy aging and mild cognitive impairment (MCI) shows promise in improving cognitive functions that are also commonly affected in HIV [22]. There is more than a conceptual parallel between these conditions. Subtle pathological aging changes are found in the brains of people with HIV [23]. We hypothesize that non-pharmacological interventions that have proved useful in aging and MCI will make a difference in mood, cognitive performance, and real world outcomes such as occupational functioning and quality of life in HIV. Here we describe the objectives, protocol and analytic plan for a project addressing key questions related to brain health in HIV using a cohort multiple randomized controlled trials design.

### Objectives

This project has three overarching aims reflecting the core goals of identifying, understanding and optimizing brain health in people living with HIV, focusing on cognitive ability, its measurement, contributors and consequences. The specific objectives are:(i)To estimate the extent to which HIV-related clinical factors and patient-centered outcomes relevant to brain health and its consequences inter-relate and evolve over time and to explore the mechanisms underpinning longitudinal change in brain health;(ii)To contribute evidence for the validity of a brief brain health assessment approach combining both patient-reported and measured cognitive deficits;(iii)To contribute evidence for the feasibility, effectiveness potential, and acceptability of promising non-pharmacological interventions for optimizing brain health.

This is an on-going study, with external funding from a competitively awarded, peer-reviewed Team Grant from the Canadian Institutes of Health Research (TCO-125272), and institutional research ethics approval (Biomedical D Research Ethics Board protocol 13–047, McGill University Health Centre).

## Methods

### Cohort design

We have developed a platform to fully characterize the heterogeneity of brain health in people with HIV, including its evolution over time and its impact. This platform also allows a sampling strategy, based on cohort multiple randomized controlled trials design [24], to identify people eligible for entering pilot studies of promising interventions. Biological specimens (serum, plasma, peripheral blood mononuclear cells, saliva for genetic analysis) are banked in anticipation of future research, including novel collaborations. The project overview is provided in Fig. 1.

**Fig. 1 Fig1:**
[figure not shown]
Overview of research platform, including the main cohort, followed longitudinally, and the strategy for sampling from this cohort for multiple randomized controlled trials of non-pharmacological interventions

### Study population

The target population is people in middle age and older, the group felt to be most at risk of both longer-term effects of HIV infection and the interaction between these and aging-related brain changes: Inclusion criteria are age ≥35, HIV+ for at least 1 year, able to communicate adequately in either French or English, and able to give written informed consent. If necessary, we will oversample patients >60 years old and women to ensure at least 100 of each are enrolled. The focus is on milder cognitive deficits, which is the area of greatest clinical uncertainty. Thus, exclusion criteria include dementia (MoCA <18) [25], or treating physician’s concern about capacity to consent, life expectancy of <3 years or other personal factor limiting the ability to participate in follow-up, non-HIV-related neurological disorder likely to affect cognition, known active CNS opportunistic infection or hepatitis C requiring Interferon-based treatment during the follow-up period, psychotic disorder, or current substance use disorder or severe substance use disorder within the past 12 months. Individuals with current or past major depressive disorder are eligible for the core project, and indeed will be the focus of one of the studies under our third aim. There are additional inclusion/exclusion criteria for individual sub-studies, described below. A brief questionnaire is used to identify characteristics of all persons approached for recruitment to determine whether non-participation introduces a selection bias into our study.

The core of the research program is the development and follow-up of a comprehensively characterized cohort of persons with HIV. The cohort is being assembled through consecutive sampling from five clinics in several large cities in Canada: Montreal, Toronto, Hamilton, and Vancouver. These clinics collectively manage thousands of patients, with diverse demographic and HIV risk profiles, most of whom are routinely followed at 3 month intervals. A total of 900 participants will be comprehensively assessed and followed longitudinally at 9 month intervals over a 3 year period (four assessments).

### Measurement strategy: the brain health platform

We will apply a theory-based measurement framework, the Wilson-Cleary outcome model, to structure this portion of the study (Fig. 2). This model is widely used to assess the life impact of medical conditions. The model comprehensively considers the relationship between characteristics of the individual, and of their environment, as they relate to a continuum from biological variables, to symptoms, to functional status and quality of life [26]. There have been three studies using the Wilson-Cleary model in HIV, with a restricted set of variables, and none including cognitive constructs [26–28]. Figure 2 and Table 1 present the constructs measured in the current study in all patients within the Wilson-Cleary framework. We have situated the brain health measures within the ‘symptom’ and ‘function’ rubrics of this model. Information on the key constructs is collected through chart review, face-to-face interviewing and direct testing, and through questionnaires. All questionnaires are brief and well known in the health literature, and widely tested in various populations, permitting comparisons across health conditions. To assure wide application to the broader clinical context, we selected measures that are in the public domain and available in English and French. The platform will serve as a sampling frame for a series of trials targeting brain health in selected sub-groups.

**Fig. 2 Fig2:**
[figure not shown]
Wilson-Cleary outcome model. Characteristics of the individual include motivation, symptom amplification; characteristics of the environment include psychological and social supports

**Table 1 Tab1:** Constructs to be measured within the structure of the Wilson-Cleary framework

Characteristics of the individual				
Age, sex, self-declared race, height, weight, education, work status, occupation, living situation, cognitive reserve indicators, coping, smoking, alcohol, drug use, healthy eating behaviour				
Biological and physiological variables	Symptom status	Functional status	Health perception	Quality of life (QOL)
Nadir CD4+, current immunological markers, current viral load, peak viral load, current ARV treatment, duration of HIV infection; Co-morbidities: diabetes, cardiovascular disease, hypercholesterolemia, hepatitis B & C, vitamin B12, thyroid-stimulation hormone (TSH), others Medications	Physical Symptoms: vitality, pain, sleep quality, HIV related signs and symptoms	Measured and self-reported cognitive deficits; cognitive ability; self-efficacy	General health perception; health utility	Personalized QOL; HIV-specific QOL
	Emotional symptoms: anxiety, stress, depression, apathy	Physical activity; physical function; self-efficacy for managing HIV health challenges		
		Role participation: work status, work quality, nature and frequency of leisure activities, life space mobility		
Social and psychological supports				
Social support, self-management priorities				

*ARV* anti-retroviral

### Primary outcome: cognitive ability

Measurement of cognitive ability using the B-CAM© (Brief Cognitive Ability Measure) is central to the platform. This computerized test battery was developed using Rasch Measurement Theory and Rasch analysis. Items from cognitive tests and self-report cognitive difficulties were co-calibrated to identify those that provided a measure of cognitive ability with linearized units so that the total score can legitimately be used mathematically to compare people on the same metric and to monitor change [29, 30]. Including both objective tests and self-report items is advantageous for eventual translation to routine clinical practice, in that self-report information is readily acquired and could be used to identify people in need of more in-depth assessment. The B-CAM takes less than 30 min to complete.

*Self-report Cognitive Concerns* will be measured using the Perceived Deficit Questionnaire (PDQ) [31]. This 20-item questionnaire (scored 0 to 80) measures cognitive lapses, with a score >40 indicating cognitive impairment. The PDQ has been used in several health conditions and healthy populations [32, 33].

#### Cognitive reference standard

The neuropsychological battery recently developed for CIHR Canadian HIV Trials Network (CTN) studies, the CTN Neurocognitive Battery, will serve as the reference standard for comparison purposes with B-CAM. This battery allows diagnosis of HAND as per the 2007 definition [3] by testing at least five cognitive domains with at least two tests per domain, while being as brief as possible. The tests are listed in Table 2 and take approximately 90 min to complete. In addition to diagnostic and feasibility considerations, tests were chosen to be available in both English and French with norms suitable for use in Canada.

**Table 2 Tab2:** Tests Included in the Reference Standard Canadian HIV Trials Network (CTN) Neurocognitive Battery

Cognitive domains	Tasks
Memory (learning/recall)	Hopkins Verbal Learning Test-Revised (HVLT-R)
	Brief Visuospatial Memory Test-Revised (BVMT-R)
Executive functioning	Tower of London
	Stroop
	Trail Making Test B/A
Attention/working memory	Letter/Number Sequencing^a^
	Spatial Span^b^
Processing speed	Digit Symbol-Coding^a^
	Symbol Search^a^
Verbal/language	Letter Fluency FAS^c^
	Category Fluency^c^
Motor	Grooved Pegboard, dominant and non-dominant hand
IQ estimation	Toni-IV

*IQ* intelligence quotient

^a^Wechsler Adult Intelligence Scale-IV (WAIS-IV)

^b^Wechsler Memory Scale-III (WMS-III)

^c^Delis-Kaplan Executive Function System (D-KEFS)

### Multiple randomized controlled trials design

All participants are provided with an information package on strategies known to have a positive effect on brain health. Our Brain Health Now Tips cover recommendations for stopping smoking, challenging the mind, limiting alcohol and street drugs, increasing physical activity, sleeping well, managing stress and negative moods, healthy eating, and the importance of telling the medical team about all current medications. In addition to this, a series of pilot interventions targeting one or more aspects of brain health are included in this study (Table 3). Each trial has its own protocol, submitted for separate ethical review. People who meet eligibility criteria are identified from the database and those from the site where the study is conducted will be offered the intervention; eligible participants from the other sites serve as controls. Two of the trials, cognitive training and the insomnia intervention, have started recruitment. For all but two of the trials, cognitive ability is the primary outcome. The trials are designed to have a common outcome definition (responder status), analysis and sample size.

**Table 3 Tab3:** Planned pilot trials for the brain health now study

Intervention	Site	Selection criteria [outcome measure]	
		B-CAM level^a^ including a self-report cognitive concern [B-CAM primary/secondary]	Other criterion
Cognitive training	Montreal	^a^[Primary]	
Insomnia intervention	All	^a^[Secondary]	Sleep dissatisfaction
Exercise	Montreal	[Primary]	Sedentary; physical function limitations
Sleep apnea intervention	Selected	[Primary]	Sleep dissatisfaction / sleep apnea screen
Goal management training	Selected	^a^[Primary]	
Cognitive behavioural therapy	Montreal	[Secondary]	Depressive symptoms
Relaxation	Montreal	[Secondary]	Anxiety

^a^indicates that selection criteria include a score lower than the mean on the B-CAM

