#### Aim 3: to contribute evidence for the feasibility, effectiveness potential, and acceptability of interventions holding promise for optimizing brain health

The analysis for all of the intervention trial cohorts is a mix of within- and among-cohort contrasts including contrasts with those eligible for selection, but not selected, who can serve as controls. We have designed these pilots to identify the proportion with a cognitive response rather than calculating an average response and comparing averages over time or between cohorts. This responder-status analysis provides more relevant information both at a group level and at an individual level. As the time frames for each pilot may be different, the definition of a responder can reflect these differences. For example, responder-status could be defined immediately post-intervention or at follow-up or both. With a simple responder-status analysis, it is possible to calculate the probability of achieving a certain responder proportion, which will be useful for designing future trials.

For between-group comparisons, logistic regression will be the global approach to analysis with responder-status (yes-no, defined the same way for intervention and control cohorts) as outcome. The exposure is cohort: intervention vs. control. The control group is likely much larger than the intervention cohorts, so comparing each cohort to the control is statistically reasonable. People may not complete all of a given intervention, which may affect opportunity for change; a restricted analysis will be conducted on those completing at least 60 % of the sessions, recognizing that power is reduced but the information nonetheless valuable for the design of future studies.

Generalized estimating equations (GEE) will also be applied as a secondary, more general approach that permits other time points to be modeled, and consideration of other outcomes. This accommodates either binary (responder status) or continuous (scores on cognitive tests) outcomes. This analysis uses a regression model, but clustering of outcomes within time is controlled. For binary outcomes, the effect of group (intervention or control) is expressed as an odds ratio; for continuous outcomes the parameter is an effect size equivalent to an adjusted paired-*t*-test. An interaction term tests whether the effect differed by group (i.e. was larger in the intervention group, as hypothesized).

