### Ethics, consent and permissions

The project was approved by Research Ethics Board of each of the participating institutions, with the caveat that the pilot trials would each have their own protocol and ethics submission. All participants provide written, informed consent at the time of enrollment in the cohort. Where deemed ethically permissible, we also collect limited information from eligible individuals who refuse participation in the study in order to estimate selection bias. The local research ethics board at one center did not approve the collection of information from refusers. For the intervention studies that are recruited through telephone or email contact and are delivered only through the Internet, no additional visit is needed. We obtained ethics approval for these intervention studies only from the center from which the study was going to be conducted, after confirmation that this approach was in compliance with the national regulatory framework in Canada.

The informed consent document stipulated that any clinical results of importance for the participant’s medical care would be provided to their physician. Most blood tests are clinically indicated and are reviewed as part of routine care. For the information collected on the questionnaires, in collaboration with the site principal investigators, we developed a list of “red flags” to identify participants who may be in serious distress. The “red flags” pertain to issues of mood, pain and quality of life, as those were considered important to medical care. On a monthly basis, answers to selected questions are extracted from the database and the participants’ physicians are alerted to the presence of worrisome self-reports.

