Chronic HIV infection poses complex challenges that are likely exacerbated by aging and the accrual of co-morbidities, and likely affect brain health through multiple paths. This project takes a multi-pronged approach to measuring cognition and mental health concerns, understanding the basis of differences in cognitive ability, and assessing potential interventions. We apply a novel approach, the cohort multiple randomized controlled trials design. Since a pivotal paper on this method was published in 2009 [24], only a handful of studies have proposed this design [44–48]. This will be the first study to use this design to test multiple interventions.

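### The pilots are labelled randomised, but the only allocation rule stated is by site, so treatment and site cannot be separated in the Montreal pilots and the rule does not fit the all-site insomnia trial

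*Protocol article*

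**What the plan says.** The abstract states "We adopt a cohort multiple randomized control trials design", and the Discussion repeats it: "We apply a novel approach, the cohort multiple randomized controlled trials design".

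The section on the multiple randomized controlled trials design gives one rule for the pilots as a group. Eligible people are found by searching the cohort's records, after which the rule reads: "those from the site where the study is conducted will be offered the intervention; eligible participants from the other sites serve as controls". Table 3 lists seven pilots: four at Montreal (cognitive training, exercise, cognitive behavioural therapy, relaxation), two at selected sites (sleep apnea, goal management training) and one at all sites ("Insomnia intervention All"). The section adds: "Two of the trials, cognitive training and the insomnia intervention, have started recruitment". It also says that each pilot has its own protocol, and that the pilots share outcome definition, analysis and sample size.

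The Aim 3 analysis section plans "a mix of within- and among-cohort contrasts". Among these it names "contrasts with those eligible for selection, but not selected, who can serve as controls". Its main between-group model is a logistic regression of responder status with cohort (intervention or control) as the exposure. The GEE is said to control clustering within time. Site is not mentioned in either model.

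**The concern.** A reader of the design label will take the between-group contrasts as protected by randomisation. Under the stated rule they are comparisons of one place with other places.

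The article gives reasons to expect that places differ. The clinics together have diverse demographic and HIV risk profiles, participants are French or English speakers, and each site's own research assistant helps administer the B-CAM. Any site difference in natural response, practice effect or follow-up would enter the estimated intervention effect with unknown sign. It would then be reported as evidence from a randomised trial.

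The rule also cannot be followed as written for the insomnia trial, which is already recruiting: if all sites deliver, no other site is left to supply controls.

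**Working it through.** **1. Is a random step described anywhere?** The design label appears in the abstract, the cohort design section, the section on the multiple trials and the Discussion. The only sentence that says who is offered an intervention and who is a control uses site. No passage describes random selection or random assignment.

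**2. Can the analysis separate treatment from site?** Let A = 1 at the delivering site and 0 elsewhere, and let γ_s be the effect of site s:

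logit P(response) = α + βA + γ_s

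Because A is determined by s, adding any constant c to β and subtracting c from γ at the delivering site leaves every fitted value unchanged. So β is not identifiable once site is in the model. If site is left out, β absorbs the difference between the delivering site and the others. More controls reduce variance but not this bias. If Montreal holds two of the five clinics (the article names four cities), A is still determined by site and the result is the same.

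**3. The article's own figures.** The sample-size text assumes 30 participants and a 10% or 20% response without intervention. Exact binomial tails:

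- P(X ≥ 7 | 30, 0.10) = 0.0258, which agrees with the stated p < 0.03.
- P(X ≥ 11 | 30, 0.20) = 0.0256 and P(X ≥ 10 | 30, 0.20) = 0.0611, so 11 is the smallest count below 0.05, as stated.

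**4. The same threshold if the delivering site's untreated rate is not 10%** (assumed rates, no treatment effect):

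| Untreated rate at delivering site | P(7 or more of 30) |
|---|---|
| 10% | 0.026 |
| 12% | 0.061 |
| 15% | 0.153 |
| 20% | 0.393 |

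**5. The two-group comparison.** Exact enumeration of a two-sided 5% pooled z-test, 30 offered, 10% response at the other sites, no treatment effect. The number of controls is assumed, because the article says only that the control group is likely much larger.

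| Controls | 10% vs 10% | 15% vs 10% | 20% vs 10% |
|---|---|---|---|
| 30 | 0.054 | 0.095 | 0.194 |
| 100 | 0.046 | 0.137 | 0.319 |
| 200 | 0.041 | 0.157 | 0.374 |

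With a site difference present, a larger control group makes a false finding more likely.

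**6. Random variation between sites instead of a fixed shift.** Simulation with the same test, 30 at one clinic against 50 at each of four others, 10% average-site response. With a between-site SD on the logit scale of 0, 0.2, 0.3 and 0.5, the false-positive rate is 4.1%, 5.3%, 6.7% and 11.5%.

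**7. Precision cost of same-site controls.** Assume 900/5 = 180 people per clinic and half below the B-CAM mean, so 90 eligible. Drawing 30 leaves 60.

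- Against 160 other-site controls (40 per clinic): √(1/30 + 1/60) / √(1/30 + 1/160) = 0.2236/0.1990 = 1.12.
- Against 360 (90 at each of four clinics, consistent with the 90 above): 0.2236/0.1900 = 1.18.

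**The case against.** Several points on the other side are fair.

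- **Not every effect is confounded.** A reader might infer that all seven pilots are compromised in this way. The documents do not support that. A trial run at all sites is not confounded with site by this rule, and the within-cohort contrasts in Aim 3 do not compare sites; their weakness is the lack of a concurrent control.
- **The insomnia trial need not lack controls.** It is tempting to conclude that it has none. That follows only from a literal reading of the site rule. The Aim 3 wording allows eligible people who were not selected, whom an all-site trial can supply, and the trial's own protocol is not shown.
- **The two descriptions of controls are compatible.** Eligible people at other sites are also eligible and not selected, so the Aim 3 wording is broader and not contradictory. What does not fit is the site rule beside the all-site row of Table 3.
- **Covariates are not excluded.** Naming cohort as the exposure does not rule out adjustment. But a site term cannot help where site and group coincide, and measured baseline factors remove only part of the difference.
- **Response concerns change.** A stable site difference in score level does not by itself bias responder status; a difference in change does. This narrows the routes to bias without closing them.
- **These are pilots**, sized on a single-group threshold. Even so, Aim 3 seeks evidence on effectiveness potential, and the abstract promises pragmatic evidence on effectiveness and comparative effectiveness.

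That each pilot has a separate protocol does not remove the problem, because this article itself fixes the site rule for the pilots as a group.

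**Conclusion.** The point holds in this limited form. The label says randomised and the only stated rule allocates by site. For the four Montreal pilots the between-group effect is fully confounded with site; for the two selected-site pilots this is so if the rule is applied there. For the insomnia trial, the rule must be reconciled with Table 3 and with the Aim 3 description of controls.

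The confounding follows from the rule alone. The size of the resulting error depends on site differences that the article does not quantify. With assumed untreated rates of 15% or 20% at the delivering site against 10%, the chance of a false success on the 7-of-30 threshold is 15% or 39% instead of 2.6%. In a comparison of 30 with 200 it is 16% or 37% instead of 4%. These figures illustrate possible bias and are not evidence that such site differences exist. The matter should be corrected before any pilot is reported as a randomised comparison.

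**What to change.** **Pilots not yet filled.** Replace the site rule with a computer-generated random draw, within each delivering site, of the eligible cohort members to be offered the intervention. Eligible members of the same site who are not drawn are the controls. Compare all offered, including those who decline, with all not offered, by logistic regression adjusted for baseline score and, where there is more than one delivering site, for site. Use eligible people at other sites only as a descriptive reference. For interventions "delivered only through the Internet, no additional visit is needed", so the draw can be made within every site.

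**Pilots already allocated by site.** Describe them as non-randomised site comparisons, adjust for baseline B-CAM, age, education and test language, and state residual site confounding as a limitation.

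**Insomnia trial.** State where its controls come from, so that the allocation sentence, Table 3 and the Aim 3 section agree.

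**Cost.** The draw uses the existing database and needs no extra visits. Same-site controls are fewer: the standard error is about 12% to 18% larger if 60 remain, and more if the added criteria in Table 3 or the overlap of four pilots at Montreal shrink the pool. Because each pilot has its own ethics review, trials under way would need an amendment or the relabelling above.
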